### Statistical analysis

A range of statistical methods will be employed to analyse the diverse quantitative and qualitative data collected throughout the study. Descriptive statistics (e.g., means, standard deviations, frequencies) will be used across all datasets to summarize key variables. For the survey data, statistical techniques such as Chi-square test, analysis of variance (ANOVA), linear regression, and Pearson correlations will be employed to assess associations between variables and differences across groups (e.g., countries, professional groups).

To assess changes over time and between intervention and control regions, longitudinal and multilevel analyses will be applied. These include a generalised linear mixed model, Binomial and Poisson Regression, Interrupted Time Series Analysis, Linear Mixed Modelling (LMM), and Repeated Measures ANOVA. Missing data in longitudinal models will be handled using the implicit imputation properties of linear mixed models, which use all available data under the missing at random (MAR) assumption and provide unbiased parameter estimates without the need for explicit imputation procedures.

Finally, qualitative data from interviews and focus groups will be audio-recorded, transcribed, and analysed using thematic analysis to identify key patterns and insights.

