## Abstract

Depression and suicide are leading public health problems requiring complex multilevel interventions. This study protocol details the COMBINA trial, which expands the evidence-based European Alliance Against Depression (EAAD) Community-Based 4-level intervention to also focus on improving wellbeing and tailored to five groups with increased vulnerability to depression: young people, older people, migrants/refugees, the long-term unemployed, and people with an existing mental health condition. In this prospective, non-randomised controlled trial, the COMBINA project will be newly implemented during a 24-month period, from late 2024 to late 2026, in five regions in Albania, Estonia, Greece, Ireland, and Spain. These regions will be compared to five control regions in the same countries, chosen to reflect a similar context, size, and sociodemographic characteristics. Main outcomes are a comparison between the intervention and control regions in the rates of deaths by suicide and hospitalisations for suicide attempts and the levels of wellbeing, depressive symptoms, anxiety symptoms, depression-related stigma, and willingness to seek psychological help in the general population. A process evaluation and economic evaluation will also be conducted. This intervention protocol also details the steps taken to promote successful implementation across a range of different cultural and regional contexts, with challenges including different existing mental health resources and differing capacities for the population to use digital tools. The COMBINA project includes co-creation, whereby materials and implementation strategy were designed with people from the vulnerable groups. The trial is funded by the European Union (grant agreement no. 101080651 and carried out according to the Declaration of Helsinki. Ethical approval has been obtained in all participating countries. The results will be published in peer-reviewed academic journals, presented at scientific meetings and disseminated through COMBINA stakeholders, with participation from the co-creators. This trial protocol (version 1.1, 24/10/2024) was registered in the ISRCTN registry (ISRCTN10521127) on 14/11/2025 (https://www.isrctn.com/ISRCTN10521127).

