**Fig 2 pone.0352598.g002:**
[figure not shown]
Protocol Overview. Cross-country study protocol flowchart illustrating the main steps: region selection (control regions are shown within boxes with dashed borders), implementation of the 4-level intervention, evaluation components, and timeline (0–24 months; Mth = months).

Process evaluation: to comprehensively investigate the context-related implementation process of the intervention, including fidelity, reach, adoption, acceptability, and contextual facilitators and barriers across diverse European settings (Albania, Estonia, Greece, Ireland, and Spain).Outcome evaluation: To examine whether the expanded four-level intervention achieves its intended outcomes through a controlled, cross-country design. The evaluation will focus on clinical outcomes (e.g., reductions in suicidal behaviour and depressive symptoms) and non-clinical outcomes (e.g., improvements in wellbeing, self-reported mental health, and attitudes toward depression and help-seeking). Additionally, pre-post assessments without a control group will be included as well.Economic evaluation: to determine the cost-effectiveness of the intervention, expressed as the observed incremental cost per unit of outcome gained: cost per death by suicide avoided, per suicide attempt avoided and per percentage point improvement in selected clinical and subclinical outcomes derived from the population surveys conducted in each site.

The effectiveness of the expanded community-based 4-level intervention will be evaluated through a prospective controlled cross-country design across five European countries – Albania, Estonia, Greece, Ireland, and Spain. In each country, one intervention region and one comparable control region will be selected to allow for between-group comparisons. Primary clinical outcomes will be collected in both intervention and control regions to assess changes in depressive symptoms, suicidal behaviour, and wellbeing. Additionally, intermediate clinical and service-related outcomes will be collected in the intervention regions only to explore mechanisms of change and evaluate the broader system-level impact of the intervention.

The process evaluation will be conducted in both the intervention and control regions, using a mixed-methods approach that integrates both quantitative and qualitative data collection measures.

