### Regions

Each participating country selected a region which was feasible and had a suitable context for implementing a large-scale community intervention. A control region was chosen to match as closely as possible the characteristics of the chosen intervention region in terms of size, level of urbanisation, and sociodemographic characteristics, to minimise selection bias. Baseline sociodemographic and mental health indicators will be collected for both regions to assess comparability and to adjust for pre-existing differences in the analyses. Population sizes were matched as closely as feasible, ranging from approximately 117,538–350,000 inhabitants across the five participating countries (see Table 1).

**Table 1 pone.0352598.t001:** Overview of intervention and control sites.

Country	Intervention area (Number of inhabitants)	Control area (Number of inhabitants)
Albania	Central Tirana (350,000)	Elbasan (252,719)
Estonia	Mustamäe & Haabersti (117,538)	Lasnamäe (119,092)
Greece	Thessaloniki municipality (324,766)	Larissa (144,651)
Ireland	Limerick City & County Council (209,536)	County Galway (277,737)
Spain	Santa Coloma de Gramenet (119,195)	Sant Marti (242,752)

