### Outcome evaluation

The outcome evaluation will primarily focus on **changes in attempted suicide rates**, operationalised as hospitalisations for intentional self-harm, comparing intervention and control regions over the 2-year implementation period. Monthly hospitalisation data for intentional self-harm will be retrospectively extracted from hospital records covering September 2019 to August 2026, from hospitals serving residents of the intervention and control regions and agreeing to provide data. **Suicides**, including deaths of undetermined intent, will be analysed as a **key secondary outcome**. Annual suicide mortality data will be obtained from national statistical offices for the years 2018–2026 and expressed per 100,000 population by gender.

Other secondary outcomes include changes in public knowledge and attitudes toward depression and its treatment, and mental wellbeing. These will be assessed through general population surveys conducted in both intervention and control regions at baseline and 24-month follow-up, with samples of 500 residents per region. The chosen sample size is consistent with earlier large-scale evaluations of the EAAD multi-level intervention [76], which successfully used regional samples of approximately 500 respondents to detect meaningful changes in depression stigma, attitudes toward help-seeking, and awareness of campaign activities across intervention and control regions. Replicating this sampling approach ensures sufficient power to detect small-to-moderate changes in our outcomes. The samples are stratified by age and gender, following predefined quota for the target population, and recruited through a mix of face-to-face interviews, telephone interviews, and online surveys. Surveys were carried out by external accredited market research agencies, to improve methodological robustness and reduce selection bias. The survey includes sociodemographic and health-related questions, and four validated scales. Below, the English language versions of the scales are described. Validated translations were used for Albanian, Estonian, Greek, and Spanish, and where no validated scale was available, a back translation process was used.

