
A key limitation of the study design is the absence of randomisation and blinding, which may introduce selection bias and limit causal inference regarding intervention effects. However, the pragmatic nature of the trial and the use of matched control regions enhance ecological validity and reflect real-world implementation conditions. Although matching and baseline adjustments will be undertaken to control for differences between intervention and control regions, residual confounding cannot be fully excluded. Systematic monitoring of adaptations using the FRAME framework will, however, help interpret these differences. Additionally, ensuring consistent implementation across all intervention sites is challenging due to variation in stakeholder engagement, and local infrastructures, which may affect fidelity and the intensity of delivery. Measurement and data comparability may also be influenced by differences in translation, cultural interpretation, and administration of survey instruments, despite rigorous harmonisation and back-translation procedures. Furthermore, the reliance on self-report data introduces the potential for social desirability bias, particularly in countries where stigma toward mental illness remains high. The study’s medium-term evaluation period may not capture long-term outcomes or sustainability effects, and differences in local funding structures and institutional support may affect reach and data completeness. Given the low frequency of deaths by suicide, it will be challenging to see enough variability in suicide rates to statistically link it to exposures. Finally, because the intervention is community-based and highly visible, spill over effects between intervention and control regions may occur, potentially diluting measurable differences.

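### Poisson and Binomial regression are offered for a five-against-five region comparison; without a region-by-period variance term, intervals for self-harm hospitalisations could be too narrow

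*Protocol article*

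**What the plan says.** The Study aims and design section sets the unit of assignment: "In each country, one intervention region and one comparable control region will be selected to allow for between-group comparisons". The Abstract confirms that allocation is not randomised. Table 1 lists the ten regions.

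The Outcome evaluation section makes attempted suicide the main outcome, "operationalised as hospitalisations for intentional self-harm, comparing intervention and control regions over the 2-year implementation period". On the data it says: "Monthly hospitalisation data for intentional self-harm will be retrospectively extracted from hospital records covering September 2019 to August 2026". That is 84 monthly points per region.

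The Statistical analysis section introduces the comparative methods with "To assess changes over time and between intervention and control regions, longitudinal and multilevel analyses will be applied", and continues: "These include a generalised linear mixed model, Binomial and Poisson Regression, Interrupted Time Series Analysis, Linear Mixed Modelling (LMM), and Repeated Measures ANOVA". It does not say which method serves which outcome, or how region or country pair enters the model.

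Elsewhere, regional baseline indicators are to be collected "to assess comparability and to adjust for pre-existing differences in the analyses" (Regions). The limitations section says that "matching and baseline adjustments will be undertaken to control for differences between intervention and control regions", and concedes that residual confounding may remain.

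**The concern.** The intervention effect is a region-by-period contrast: the change in the intervention regions minus the change in the control regions. Its uncertainty has two parts. One is counting error, which shrinks as admissions accumulate. The other is region-specific change between periods that has nothing to do with the intervention, and this shrinks only with more regions. There are five pairs.

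Ordinary Poisson or Binomial regression carries only the first part. A mixed model with just a region intercept does little better: the intercept absorbs stable differences in level, which largely cancel in a before/after contrast, and leaves the drift out.

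The article itself gives reasons to expect drift. Under Regional adaptations it describes mental health reforms with uneven regional coverage in Greece and Albania, and data on suicide attempts of varying availability and quality. Under Outcome evaluation, only hospitals that agree will supply data. Any of these can move one region of a pair and not the other. At stake is whether the primary analysis could report local drift as an intervention effect.

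**Working it through.** The article states no alpha, event rate, effect size or between-region variance for the primary outcome, so there is no figure to reproduce. The check asks how a nominal 5% Poisson test behaves when there is no true effect.

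**Inputs from the article**
- Populations (Table 1), intervention / control: Albania 350,000 / 252,719; Estonia 117,538 / 119,092; Greece 324,766 / 144,651; Ireland 209,536 / 277,737; Spain 119,195 / 242,752.
- Data window: 84 months.

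**Assumptions (not in the article)**
- 60 months before and 24 months during the intervention.
- Admission rate r of 50, 100 or 200 per 100,000 per year in all regions.
- SD τ of each region's log-rate change unrelated to the intervention; main value 0.05.

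**Step 1: Poisson variance.** For country j, the estimate is log(during/before) in the intervention region minus the same in the control region. Its Poisson variance is (1/5r + 1/2r)(1/N_I + 1/N_C) = 0.7/(r·M_j), with M_j = N_I·N_C/(N_I + N_C). M_j is 146,754 (Albania), 59,155 (Estonia), 100,077 (Greece), 119,432 (Ireland) and 79,942 (Spain), total 505,360. Inverse-variance pooling gives a variance of 0.7/(r × 505,360). At 100 per 100,000 this is 700/505,360 = 0.001385, so the reported SE is 0.0372.

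**Step 2: add drift.** The weights p_j are 0.290, 0.117, 0.198, 0.236 and 0.158, and Σp_j² = 0.218. Drift in both regions of each pair adds 2τ² × 0.218. At τ = 0.05 that is 0.00109. The true variance is 0.001385 + 0.00109 = 0.00248, so the SD is 0.0498, which is 1.34 times the reported SE.

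**Step 3: real type I error** = 2(1 − Φ(1.96/k)), where k is true SD divided by reported SE. For k = 1.34 this is 14%.

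| Rate per 100,000 per year | No drift | SD 0.05 in the change | SD 0.05 in each period |
|---|---|---|---|
| 50 | 5% | k = 1.18, 10% | k = 1.34, 14% |
| 100 | 5% | k = 1.34, 14% | k = 1.60, 22% |
| 200 | 5% | k = 1.60, 22% | k = 2.04, 34% |

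The last column doubles the drift variance, because the change then contains two independent deviations.

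**Cross-check by simulation** (20,000 runs per cell). Pair-wise pooling at SD 0.05 in the change gives about 9–21%, in line with the formula. Summing counts over regions before taking the rate ratio gives 11–25% at SD 0.05 and 26–50% at SD 0.10. With no drift it gives 4.8–5.2%.

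**Region-level alternatives.** In the same simulations, a t test on five against five region-level log changes (8 df, critical value 2.31) and a paired t test on five countries (4 df, critical value 2.78) both stay at 4.4–5.3%. At 100 per 100,000, power for an assumed rate ratio of 0.80 is 0.96 (8 df) and 0.88 (4 df) at SD 0.05, and 0.73 and 0.60 at SD 0.10.

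**Survey outcomes.** There are 500 respondents per region, so 2,500 per arm per wave. The design effect is 1 + 499 × ICC. At an assumed ICC of 0.01 it is 5.99, the effective size is 2,500/5.99 = 417 per arm, and power for an assumed standardised difference of 0.2 at one wave is Φ(0.2 × √(417/2) − 1.96) = 0.82. Ignoring clustering, it exceeds 0.999. At ICCs of 0.005 and 0.02 it is 0.97 and 0.57. These are normal approximations, so optimistic with five regions per arm.

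**The case against.** The strongest reply is that the article commits to no error. Its list is introduced as longitudinal and multilevel and begins with a generalised linear mixed model. The Poisson and Binomial entries might name an outcome family within that model, or be meant for suicide counts or dichotomised survey items. Random-effect structure and degrees of freedom usually belong in an analysis plan, which is not shown here. This stands in part: a reader might infer that a plain Poisson model is fixed for the primary outcome, and the text does not say so. What remains is that Poisson and Binomial regression are named for exactly the intervention-control comparison. An analysis plan could follow the sentence faithfully and still use a variance that omits drift, and a mixed model with only a region intercept would satisfy the multilevel wording without curing it.

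A reader might also infer that adjusting for regional baseline indicators makes the intervals too narrow, or that the authors claim it settles confounding. Neither is supported. None of the calculations includes covariates, and the limitations section itself admits residual confounding. The limit is a different one: ten regions can support only very few region-level covariates. Individual-level adjustment of the survey data is unaffected.

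Nor does the article say whether repeat admissions of one person are counted, so overdispersion from that source is a possibility and not a documented fact.

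Finally, the numbers depend on rates and drift that the article does not give. That is true, and with no drift the Poisson test is correct.

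**Conclusion.** The point holds conditionally. The article places methods with and without a suitable variance side by side for a comparison that rests on five non-randomised pairs. If an ordinary Poisson or Binomial model, or a mixed model with only a region intercept, is applied to self-harm hospitalisations, the interval could be too narrow. With drift of about 5% per region, a nominal 5% test would err roughly two to four times as often as stated (10–22%), and up to about a third of the time if drift of that size occurs in each period. These sizes rest on the assumed admission rates, drift SDs and 60/24-month split. The direction does not: any region-specific drift makes the Poisson interval too narrow.

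**What to change.** For the primary intervention effect, name one analysis with region or country pair as the unit of inference. Either of these would serve:

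- a generalised linear mixed model with region-by-period random variance, an allowance for overdispersion, and small-sample degrees of freedom; or
- one difference-in-differences log rate ratio per country, the five combined with a small-sample t interval. Four degrees of freedom apply if the analysis is paired. Eight apply if the ten region-level changes are compared unpaired. Both hold the error rate; the unpaired version had more power in the simulations, which built in no shared country-level drift.

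Show the five country estimates. State that Poisson or Binomial regression without a region-by-period variance term will not be used for this effect. Apply the same region-level inference to the survey comparisons. Keep any region-level covariate list very short and pre-specified.

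An exact sign-flip test on five pairs is not a substitute, since its smallest two-sided p-value is 2/2⁵ = 0.0625.

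The change is to analysis wording only; no further data are needed. The price is wider intervals (critical value 2.31 or 2.78 in place of 1.96, on a larger standard error where drift exists) and lower power, as shown above.

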### Dissemination

The results of this study will be disseminated through scientific publications in high-ranking peer reviewed journals, as well as through scientific conferences, and shared in lay language with stakeholders from the intervention regions. Co-creators will be involved in the dissemination process.

## Discussion

### Regional adaptations

The five COMBINA countries differ in terms of culture, economy, and existing mental health services and infrastructure, creating challenges for the successful implementation of this protocol, and highlighting the need for the protocol to be adaptable to each setting [81]. The project will draw from extensive experience in implementing the Community-Based 4-Level Intervention concept and building local alliances in over 120 regions across 15 countries in order to successfully implement the intervention in the different settings [82].

Mental health services vary significantly across different European countries in terms of care availability and capacity [83]. Implementation of the COMBINA intervention may be affected by variations across the five participating countries in a range of domains. Firstly, in terms of health system organisation and primary care capacity, Ireland and Spain have national suicide prevention strategies and community mental health frameworks that align well with the EAAD model [84,85]. Greece and Albania are currently implementing mental health reforms with variable funding and regional coverage, which may affect institutional buy-in [86,87]. Estonia has robust digital health policies but limited workforce capacity in mental health, posing potential implementation barriers [88,89].

Secondly, there are regional differences in cultural attitudes and stigma. Stigma toward mental illness and help-seeking remains relatively high in Albania and Greece [90,91]. Ireland and Spain demonstrate greater public openness to discussing mental health and support for community-based promotion [92–94]. Social stigma in Estonia, particularly in men, around mental health may be a barrier to help-seeking behaviours [95]. Thirdly, the economic and social context differs across countries. Economic instability and unemployment rates are higher in Greece and Albania, wh.-ich may exacerbate psychological distress but also increase the relevance of preventive initiatives [96,97]. Ireland and Spain face persistent urban–rural inequalities in access to mental health services, while Estonia’s smaller population and high digital connectivity may enable more targeted outreach [98–100].

Furthermore, the 4-level intervention includes several digital components and there are important differences in digital literacy and access across the regions.

Estonia has high digital literacy and extensive integration of online public services, offering fertile ground for digital mental health interventions [98]. Ireland and Spain show moderate to high digital engagement, whereas Greece and Albania have lower digital access and literacy, especially in rural or older populations [101,102], necessitating greater reliance on in-person communication strategies.

Finally, there are differences regarding stakeholder engagement and community infrastructure. Spain and Ireland benefit from well-established community networks and civil society [103,104] organisations that can act as facilitators for local implementation [105]. In contrast, Greece, Albania, and Estonia may rely more heavily on institutional or municipal structures rather than non-governmental organisations, which could influence the reach and flexibility of community engagement activities [106].

Due to these regional differences, this protocol is designed to be flexible, so that the intervention can be adapted to the local context and integrated into the existing services and networks while focusing on the gaps in existing services where the EAAD resources can be of most use, while maintaining the key four-level elements across each country. This cross-country implementation also enables shared learning, allowing adaptation strategies developed in one setting to inform implementation in others.

Operational challenges include variability in availability and quality of data related to deaths by suicide and attempted deaths by suicide, ethical review timelines, and local capacity for training delivery, which were addressed through flexible planning and bi-weekly cross-country coordinating meetings.

